# Efficacy and safety of umbilical therapy with the traditional Chinese medicine formulation *Lishui Xiaogu* cataplasm for cirrhotic ascites: protocol for a randomized controlled trial

**DOI:** 10.1186/s13063-019-3221-y

**Published:** 2019-02-13

**Keywords:** Cirrhotic ascites, *Lishui Xiaogu* cataplasm, Traditional Chinese medicine, Umbilical therapy, Randomized controlled trial

## Abstract

**Background:**

Ascites is one of the most common complications of cirrhosis. Umbilical therapy with traditional Chinese medicines has been increasingly prescribed to treat cirrhotic ascites. However, high-quality evidence from clinical trials supporting such application of traditional Chinese medicines remains limited. Therefore, we designed a clinical trial to evaluate the efficacy and safety of umbilical therapy with the *Lishui Xiaogu* cataplasm formulation applied to treat cirrhotic ascites.

**Methods/design:**

This ongoing study is a double-blind, randomized, parallel, placebo-controlled trial. A total of 82 patients will be recruited and randomly assigned to either a treatment group or a placebo group, in a 1:1 ratio. The treatment group will receive umbilical therapy with the *Lishui Xiaogu* cataplasm plus red light irradiation along with conventional treatment; the placebo group will receive umbilical therapy with a placebo cataplasm plus red light irradiation along with conventional treatment. Interventions for both groups will be administered once daily for up to 10 days, with a 30-day follow-up after the last treatment. The primary efficacy measurement will be ascites depth. Secondary efficacy measurements will include abdominal perimeter, weight, urine volume, the symptomatic score of traditional Chinese medicine, and the Chronic Liver Disease Questionnaire. Adverse events will also be reported.

**Discussion:**

This randomized trial will be the first rigorous study designed to evaluate the efficacy and safety of umbilical therapy with *Lishui Xiaogu* cataplasm applied for cirrhotic ascites.

**Trial registration:**

Chinese Clinical Trial Registry, ChiCTR-INR-16007686. Registered on 1 January 2016.

**Electronic supplementary material:**

The online version of this article (10.1186/s13063-019-3221-y) contains supplementary material, which is available to authorized users.

## Background

Liver cirrhosis is a diffuse hepatic process, characterized by fibrosis and structurally abnormal nodules, representing the final histological change due to various chronic liver diseases [1]. Ascites is the most common complication of decompensated cirrhosis, which is often associated with a poor prognosis and impaired quality of life. Mortality among patients with cirrhotic ascites is approximately 40% at 1 year and 44–85% at 5 years [2, 3]. In the absence of proper treatment, large ascites may lead to dyspnea, umbilical hernia, acid–base disturbances, hepatic encephalopathy, hepatorenal syndrome, and even death.

In recent years, a series of clinical practice guidelines regarding the management of ascites has been published [4–6], providing recommendations for ascites treatment including diuretic therapy, large-volume paracentesis, and albumin infusion. However, some limitations remain, particularly concerning the side-effects of the standard treatment for refractory ascites. Therefore, it is crucial to find better practices to successfully manage ascites.

Traditional Chinese medicine (TCM), including internal and external therapeutic approaches, has been used to treat ascites for over 1000 years. According to the meridian–collateral and visceral theories of TCM, the application of herbal remedies to the umbilical region, covered and fixed with a medical gauze and adhesive tapes, along with hot ironing, can play an important role in the treatment of various diseases, including cirrhotic ascites [7]. Previous studies have reported the use of umbilical therapy to treat ascites [8, 9]. However, they lacked a rigorous trial design. Moreover, a previous study performed by our group has demonstrated a significant effect of *Lishui Xiaogu* (LSXG) cataplasm treatment for ascites. Therefore, we designed the present randomized controlled trial (RCT), which obtained special support from the Beijing Capital Characteristic Clinical Application Research Project by the Beijing Municipal Science & Technology Commission of China. Our aim is to evaluate the efficacy and safety of the LSXG cataplasm umbilical therapy in patients with cirrhotic ascites, using a rigorous prospective randomized controlled clinical trial. The findings of this trial may establish the corresponding operational criteria and obtain evidence-based medical evidence, so as to provide an effective alternative measure for the treatment of cirrhosis ascites.

## Methods/design

### Study design and setting

This ongoing study was designed as a central-randomized, double-blind, parallel, placebo-controlled, multicenter trial. The study was designed using the Consolidated Standards of Reporting Trials (CONSORT) 2010 guidelines [10]. Also, we designed the trial based on the Standard Protocol Items: Recommendations for Interventional Trials (SPIRIT) statement. The study is being performed in three centers in China, namely: Dongzhimen Hospital, affiliated to Beijing University of Chinese Medicine; Beijing Tongzhou District Hospital of Traditional Chinese Medicine; and Beijing Pinggu Hospital of Traditional Chinese Medicine. Patients with cirrhotic ascites, who meet the inclusion criteria, will be allocated in a 1:1 ratio to either a LSXG group or a placebo group. Patients in the LSXG group will receive umbilical therapy with the LSXG cataplasm plus red light irradiation along with conventional treatment; patients in the placebo group will receive umbilical therapy with a placebo cataplasm plus red light irradiation along with conventional treatment. Based on clinical experience, the treatment will be administered once daily for up to 10 days, with a 30-day follow-up after the last treatment. The depth of ascites will be assessed as the primary outcome measurement. The abdominal perimeter, body weight, urine volume, the symptomatic score of TCM, and the Chronic Liver Disease Questionnaire (CLDQ) will be used as secondary outcome measurements. All assessments will be conducted at three time points: at baseline, after the last treatment, and after the 30-day follow-up period. The flow chart is shown in Fig. 1. We also provide the Standard Protocol Items: A Recommendations for Interventional Trials (SPIRIT) figure (Fig. 2) and the corresponding checklist (Additional file 1).

**Fig. 1 Fig1:**
[figure not shown]
Flowchart of the study design. LSXG *Lishui Xiaogu*

**Fig. 2 Fig2:**
[figure not shown]
The schedule of enrolment, interventions, and assessments. LSXG *Lishui Xiaogu*, TCM traditional Chinese medicine

### Ethics

The study protocol has been approved by the Institutional Review Board of Dongzhimen Hospital, affiliated to the Beijing University of Chinese Medicine (No. ECPJ-BDY-2015-69), and has been registered with the Chinese Clinical Trial Registry (ChiCTR-INR-16007686). The Institutional Review Board will be responsible for supervising all procedures of the study, including patient recruitment, randomization, treatment administration, data storage, and so on. In the case of any changes to the original study protocol, a written application will be submitted to the Institutional Review Board for approval. The study will be conducted according to the Good Clinical Practice Guidelines and the principles of the Declaration of Helsinki. Results will be reported according to the same guidelines.

### Randomization and allocation concealment

The randomization sequence will be generated using SAS software, version 9.4 (SAS Institute). The central randomization system used in this trial was provided by the Institute of Basic Research in Clinical Medicine, China Academy of Chinese Medical Sciences. It is an online platform. Each center staff member logs into the website when the participant is enrolled, enters the basic information of the participant, and then obtains a random number. Eligible participants will be randomly assigned to the LSXG or the placebo group in a ratio of 1:1. All eligible participants will obtain the corresponding umbilical drug according to their random number, and they will be individually treated to prevent communication. The participants, researchers, and statisticians will be blinded to treatment allocation.

### Informed consent

Prior to the study, the general study process and the responsibilities of the participants and researchers will be explained to potential participants. Participants will be informed that their entry into the trial is entirely voluntary and that they can withdraw at any time. In the event of their withdrawal, data collected on the participant will not be erased and will be used in the final analyses. Written informed consent will be obtained from each participant before they undergo any interventions related to the study.

### Inclusion criteria

Participants who meet the following criteria will be included in the study:Presence of grade 2–3 ascites according to the diagnostic standards of liver cirrhosis [5]: cirrhosis patients with symmetrical distension of the abdomen, and ascites depth > 3 cm.Age between 18 and 75 years, irrespective of sex.An agreement to voluntary participation in the trial and the provision of informed consent.

### Exclusion criteria

Participants who meet any of the following criteria will be excluded:Presence of liver cirrhosis decompensation accompanied by bleeding, gastrointestinal hemorrhage, hepatic encephalopathy, hepatorenal syndrome, and other serious complications.Presence of a combination of severe cardiovascular, lung, kidney, neuronal, and blood circulation system diseases as well as other serious illnesses, such as mental illness, or tumors.Current or planned pregnancy, or nursing mothers.Presence of allergic constitution, or a past medical history of allergies to umbilical drugs or their known components.Participation in other clinical trials within 1 month before our study.

### Exclusion criteria

#### Rejection

Participants who meet any of the following exclusion criteria will be rejected:Not following the inclusion criteria.Dropout during the observation period, without any data recorded.Discontinuation of treatment following the baseline time.

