#### Discontinuation

Participants who meet any of the following exclusion criteria will be discontinued:Discontinuation of treatment.Occurrence of serious adverse events (AEs) related to the research medication.Occurrence of serious complications, such as gastrointestinal hemorrhage, spontaneous peritoneal inflammation, primary hepatic carcinoma, hepatic encephalopathy, and hepatorenal syndrome.Worsening of disease, which will require emergent treatment.Termination of the trial by the administrative authorities.

Reasons for discontinuation will be recorded on case report forms (CRFs), and the last data recorded for such participants will be included in the data analysis.

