#### Dropout

Participants can voluntarily withdraw at any time during the trial. Participants who meet the inclusion criteria, provide a completed and signed consent form, and successfully enter the randomized trial but fail to complete the proposed observational period, regardless of time and reason, will be regarded as dropout cases. Dropout cases include:Poor treatment compliance (< 80%), use of forbidden medicines, or change in treatment without consent from the study supervisor.Voluntary withdrawal or incomplete clinical data, affecting the evaluation of efficacy and safety.Occurrence of serious AEs or complications, resulting in the discontinuation and unblinding of the treatment.

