### Statistical analysis

The data from all participating centers will be combined for statistical analysis of the primary and secondary outcomes as well as the AEs. The statistical analysis will be performed at the Institute of Basic Research in Clinical Medicine, China Academy of Chinese Medical Sciences. The primary outcome will be analyzed according to the intention-to-treat principle. To compare the difference between two groups, independent *t* tests (or the Mann–Whitney *U* test) will be used to analyze continuous data and the chi-squared or Fisher’s exact test will be used for categorical data. Repeated-measures ANOVA will be used to account for the time effect.

For all measures, two-sided *p* < 0.05 will be considered statistically significant. Statistical analyses will be performed using SAS software version 9.4 (SAS Institute, Cary, NC, USA).

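### Rejecting participants who stop treatment after baseline conflicts with the intention-to-treat analysis and with the rule that keeps their data

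*Protocol article*

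**What the plan says.** Five places in the protocol article bear on a randomised patient who stops treatment.

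- **Rejection**, under Exclusion criteria, opens: "Participants who meet any of the following exclusion criteria will be rejected". Its third item is "Discontinuation of treatment following the baseline time". Its second item is "Dropout during the observation period, without any data recorded". The article does not define what rejection means for the analysis.
- **Discontinuation** also lists stopping treatment as its first criterion, followed by related serious adverse events, serious complications, and "Worsening of disease, which will require emergent treatment". For these participants, "the last data recorded for such participants will be included in the data analysis".
- **Dropout** labels as a dropout any randomised participant who does not complete observation. Its examples include "Poor treatment compliance (< 80%), use of forbidden medicines, or change in treatment without consent from the study supervisor". It does not say how dropouts enter the analysis.
- **Informed consent** says that after withdrawal "data collected on the participant will not be erased and will be used in the final analyses".
- **Statistical analysis** says: "The primary outcome will be analyzed according to the intention-to-treat principle". No modified definition of intention to treat is given.

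**The concern.** Stopping treatment after baseline is a ground for rejection in one section. In the next, it is a reason to keep the participant's last data. If rejection means leaving the analysis, a patient who stops on day 4 is out under one rule and in under the other. Only the second agrees with an intention-to-treat analysis.

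The event occurs after randomisation and, by the article's own account, may depend on treatment or outcome. The application instructions have the cataplasm removed if it causes a skin reaction, and the placebo contains only 1% of the active formulation. Worsening disease and serious complications also end participation. Excluding such patients gives up the protection of randomisation: the groups compared are those who stayed on treatment, and they may differ between arms for reasons other than the treatment effect. The result would still be reported as intention-to-treat.

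**Working it through.** **1. The rules side by side, for a randomised patient who stops treatment after baseline**

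| Section | Consequence stated | Agrees with intention to treat? |
|---|---|---|
| Rejection, third item | Rejected | No, if this means leaving the analysis |
| Discontinuation | Last data included | Keeps the patient |
| Informed consent | Data already collected are used | Keeps those data |
| Dropout | Label only | No consequence stated |
| Statistical analysis | Intention to treat for the primary outcome | Reference rule |

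The conflict is the Rejection item against Discontinuation, Informed consent and Statistical analysis. Discontinuation and Dropout do not conflict with each other: one patient can be both discontinued and labelled a dropout.

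**2. The plan's own figure**

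Inputs from Sample size: 87.5% against 62.5%, one-sided α = 0.05, power 80%, dropout 10%. With pooled variance and mean proportion 0.75:

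n = [1.645 × √(2 × 0.75 × 0.25) + 0.842 × √(0.875 × 0.125 + 0.625 × 0.375)]² / 0.25² ≈ 36.03, rounded up to 37 per arm.

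Then 37 × 1.10 = 40.7, or 41, which is the stated figure (37 / 0.90 = 41.1 would give 42). The figure is not challenged here. It supplies the 41 per arm used below.

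**3. Size of the possible bias**

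The article gives no stopping rate by arm, so the shares and the gap below are assumptions. Score the outcome so that higher is better, in SD units, with no true effect. Let e be the share excluded in an arm and g the amount by which stoppers are worse than stayers.

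Randomisation gives both arms the same overall mean μ = (mean of stayers) − e × g, so the mean of stayers is μ + e × g. With the same g in both arms:

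bias = (e for LSXG − e for placebo) × g

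- 15% and 5%, g = 1: (0.15 − 0.05) × 1 = +0.10 SD
- 20% and 5%, g = 1: +0.15 SD
- 20% and 5%, g = 1.5: 0.15 × 1.5 = +0.225 SD
- 5% and 15%, g = 1: −0.10 SD
- 10% and 10%, same g: 0
- any shares, g = 0: 0

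The 15% and 5% case averages 10%, the overall dropout the plan allows for. The article does not say that dropouts and rejected patients are the same people.

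**4. Effect on the type I error** (two-sided 5%, normal approximation, unit SD)

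For 15% and 5%: 41 × 0.85 = 34.85 and 41 × 0.95 = 38.95 are analysed.

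SE = √(1/34.85 + 1/38.95) = 0.233, and 0.10 / 0.233 = 0.429.

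Rejection probability = P(Z > 1.96 − 0.429) + P(Z < −1.96 − 0.429) = 0.063 + 0.008 = 0.071.

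The same steps give 0.097 for 20% and 5% at 1 SD, and 0.158 at 1.5 SD. With 5% and 15% the probability is again 0.071, with most false positives now favouring placebo.

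**5. Two cross-checks**

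- *Responder scale.* Take 62.5% success in both arms and suppose all excluded patients are failures. With 15% and 5% excluded, 0.625/0.85 = 73.5% against 0.625/0.95 = 65.8%, a spurious +7.7 points. With 5% and 15% it is −7.7 points. With 10% and 10% it is 0.
- *Extreme case.* Simulating 20,000 null trials of 41 per arm and removing the worst patients first gave 0.16 SD and about 15% type I error at 15% and 5%, against about 4.8% with nobody removed. At 10% and 10% the bias was nil but the type I error was about 8%, because cutting off the worst tail shrinks the SD used in the test.

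**The case against.** The strongest reply is that the Rejection section is loosely worded and that the intention-to-treat sentence governs. Rejection is undefined, and the section names no analysis set. The neighbouring item concerns participants with no data, so the third item might mean stopping directly after baseline with nothing measured later. That would largely reconcile it with Discontinuation. This reading is possible, but the words set no limit on how soon after baseline. Exclusion from the analysis is the natural reading, because the item stands under Exclusion criteria and contrasts with the explicit inclusion of last data in the next section. A separate analysis plan could settle the matter only by overriding one of the stated rules.

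A reader might infer several stronger points that the article does not support:

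- *That all three sets of rules remove patients.* Discontinuation says the opposite, and Dropout only attaches a label. Recording poor compliance or forbidden medicines as dropout is compatible with intention to treat.
- *That the article promises to use all data.* Informed consent covers data already collected from those who withdraw, and the intention-to-treat sentence covers the primary outcome only.
- *That the analyst could pick the rule that suits the active arm.* Randomization and allocation concealment blinds the statisticians. Some allocations may become known, since Dropout mentions unblinding after serious events, but an arm-aware choice is not the main risk. Exclusion on a post-randomisation event can bias the comparison even when applied blind.
- *That the bias favours LSXG.* No rates by arm are given. The Discussion describes adverse reactions as rare and links them to the plaster. If worsening drives stopping and the treatment works, placebo would lose more patients and the bias would run against LSXG. A patient who stops for a skin reaction need not have worse ascites.

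**Conclusion.** The third rejection item is wrong as written. On its natural reading it contradicts the intention-to-treat primary analysis, the inclusion of last data after discontinuation, and the use of data from withdrawn participants. The contradiction rests on the text alone and needs no assumption beyond that reading of an undefined term.

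The size of any bias cannot be derived from the article. Under the assumed 15% and 5% with a 1 SD gap it is 0.10 SD, with a type I error of about 7%. More unequal or more informative exclusion gives more. The sign reverses if placebo loses more patients, and the bias is zero if removal is equal and non-informative. The figures show that the wording could matter in a trial of 41 per arm. They do not forecast what will happen.

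**What to change.** Before unblinding:

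1. Delete stopping treatment after baseline as a ground for rejection.
2. State that every randomised participant is analysed in the assigned group for ascites depth, regardless of treatment stopping, compliance or forbidden medicines, using all ascites-depth data collected, including any measured after stopping.
3. Use the compliance below 80% and forbidden-medicine categories only to define a supportive per-protocol set.

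The clinical criteria for stopping treatment are not at issue, and the sample size does not change.

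The cost is a wording amendment plus some missing-data work. Trial status reports 78 participants against a target of 82, so some may already have left observation without an ascites depth after the 10-day intervention or at the end of follow-up. Those values may not be recoverable, and the analysis will have to handle them. The estimate may move in either direction compared with an analysis that excludes stoppers.

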#### Discontinuation

Participants who meet any of the following exclusion criteria will be discontinued:Discontinuation of treatment.Occurrence of serious adverse events (AEs) related to the research medication.Occurrence of serious complications, such as gastrointestinal hemorrhage, spontaneous peritoneal inflammation, primary hepatic carcinoma, hepatic encephalopathy, and hepatorenal syndrome.Worsening of disease, which will require emergent treatment.Termination of the trial by the administrative authorities.

Reasons for discontinuation will be recorded on case report forms (CRFs), and the last data recorded for such participants will be included in the data analysis.

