### Primary outcomes

The primary outcome measurement will be the depth of ascites. It will be measured at baseline using B-ultrasound, after the intervention (10 days), and at the end of the 30-day follow-up period.

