### Secondary outcomes

Secondary outcome measurements include the abdominal perimeter, body weight, the 24-h urine volume, the symptomatic score of TCM, and the CLDQ, which will be measured at baseline, after the intervention (10 days), and at the end of the 30-day follow-up period. The abdominal perimeter, weight, and 24-h urine volume will be measured every day from the baseline to the end of the 30-day follow-up period. The symptomatic score of TCM contains the patient’s primary symptoms, such as abdominal distension, appetite, level of exhaustion, normal/abnormal defecation, and so on. The CLDQ is a disease-specific tool designed to assess health-related quality of life in patients with chronic liver disease [15].

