### Adverse events

All unexpected AEs occurring during the intervention period will be reported, and the causality related to the LSXG cataplasm will be analyzed. If any adverse event occurs, the study managers will ensure that the participant receives adequate treatment. The AEs will be immediately reported to the principal investigator and to the ethics committee to decide whether the participant should withdraw from the trial. If any symptoms aggravate, the patient will be withdrawn from the study and will be referred for further treatment.

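### Patients withdrawn for worsening or complications enter the primary analysis with their last recorded depth or, on another reading, are removed; either way their worsening is lost

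*Protocol article*

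**What the plan says.** The relevant rules are spread over several sections of the Protocol article.

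- **Discontinuation.** The reasons include serious complications, drug-related serious adverse events and "Worsening of disease, which will require emergent treatment". For these participants, "the last data recorded for such participants will be included in the data analysis".
- **Adverse events.** "If any symptoms aggravate, the patient will be withdrawn from the study and will be referred for further treatment". This takes the patient out of the study, not only off the cataplasm.
- **Primary outcomes.** Ascites depth is the only primary measure, and the section fixes three scans for it: "It will be measured at baseline using B-ultrasound, after the intervention (10 days), and at the end of the 30-day follow-up period".
- **Secondary outcomes.** "The abdominal perimeter, weight, and 24-h urine volume will be measured every day". Depth is not among the daily measures.
- **Study design and setting.** Assessments take place "at baseline, after the last treatment, and after the 30-day follow-up period", and treatment lasts at most 10 days.
- **Rejection** (under Exclusion criteria). Stopping treatment after baseline is listed as a reason to reject a participant.
- **Dropout.** Anyone randomised who does not complete observation counts as a dropout, including those stopped for serious events or complications.
- **Statistical analysis.** "The primary outcome will be analyzed according to the intention-to-treat principle".

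**The concern.** Patients who deteriorate leave the study, so no later depth is expected from them, and an earlier value stands in for the missing one. A patient stopped on day 5 with more fluid than at entry would usually be analysed as unchanged. A patient stopped during follow-up would be analysed at the end of follow-up with the day-10 depth, which hides later worsening. Someone who stops for a skin reaction while improving on diuretics is also frozen at an old value.

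The reasons for leaving are related to the disease under study and could differ between arms. If they do, the comparison of mean depth is biased, and a single filled-in value is treated as if it had been observed. Stating intention to treat does not cure this: the patients are counted, but their outcome is not measured.

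The same patient can also fall under Rejection, Discontinuation and Dropout, and these labels do not lead to the same handling.

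**Working it through.** **1. Scale of loss in the plan.** The protocol gives no depth SD, expected depth effect or rate of worsening. Its only relevant figures are 41 per group and 10% dropout (Sample size). These reproduce. For 87.5% against 62.5%, one-sided α = 0.05, power 80% and no continuity correction:

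n = [1.645·√(2·0.75·0.25) + 0.842·√(0.875·0.125 + 0.625·0.375)]² / 0.25² ≈ 36.03, so 37 per group.

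Then 37 × 1.1 = 40.7, so 41 (dividing by 0.9 gives 42). Ten percent of 41 is about 4 patients per arm, for all reasons together.

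**2. Which depth is last on record?**

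| Time of stopping | Last scheduled depth | Effect if carried forward |
|---|---|---|
| Before the day-10 scan | Baseline | Change = baseline − baseline = 0, whatever happened |
| During follow-up | Day 10 | Day-10 result correct; later worsening hidden |

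The first row changes only if the wording in Study design and setting means a scan at early stopping. Primary outcomes ties that scan to 10 days, and no early-stopping scan is stated.

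**3. Size under carry-forward.** Let p be the share of an arm carried forward and g the mean of (true depth − carried depth) in that share. The error in the LSXG minus placebo difference is

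error = −(p_T·g_T − p_C·g_C).

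Negative values favour LSXG. All inputs below are assumed, with g equal in both arms.

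| p_T, p_C | g | Error |
|---|---|---|
| 15%, 5% | 1 SD | −0.10 SD |
| 15%, 5% | 1, 2, 3 cm | −0.1, −0.2, −0.3 cm |
| 5%, 15% | 1, 2, 3 cm | +0.1, +0.2, +0.3 cm |
| 20%, 0% | 1, 2, 3 cm | −0.2, −0.4, −0.6 cm |
| 10%, 10% | any | 0 |

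In SD units, loss differences of 5 to 15 points and gaps of 1 to 1.5 SD give 0.05 × 1 = 0.05 SD up to 0.15 × 1.5 = 0.225 SD. A split of 15% against 5% is about 6 against 2 patients out of 41.

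**4. Size if the patients are rejected instead.** Suppose completers change by −2.0 cm (LSXG) and −1.5 cm (placebo), early stoppers truly change by +1 cm, and their shares are 15% and 5% (all assumed).

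- True difference: (0.85·(−2.0) + 0.15·1) − (0.95·(−1.5) + 0.05·1) = −1.55 − (−1.375) = −0.175 cm.
- Carry-forward: 0.85·(−2.0) − 0.95·(−1.5) = −0.275 cm, an error of −0.10 cm.
- Rejection: −2.0 − (−1.5) = −0.50 cm, an error of −0.325 cm.

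Neither reading recovers the worsening, and in this example rejection does more harm.

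**The case against.** The strongest reply is that the text does not settle what happens to these patients, and several firmer readings go beyond it.

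- **That early worsening is certainly scored as no change.** A reader might infer this, but carry-forward is not named. The sentence could mean only that data already collected are kept, as Informed consent also says. The Rejection list may remove the same patients, and a scan at early stopping is a possible reading. These points stand. They make a zero change the usual result of following the text, not a certain one, and they add a contradiction that itself needs resolving.
- **That withdrawal is defined by the primary outcome.** It is not. The triggers are worsening that needs emergent treatment, drug-related serious events, complications and aggravated symptoms; none is a depth threshold. Depth after emergent treatment could be higher or lower than the carried value.
- **That the trial is biased towards LSXG, or that the type I error is inflated.** Neither follows. The direction depends on which arm loses more patients and why. If the cataplasm affected nothing at all, randomisation would make shares and gaps equal in expectation, and the false-positive rate would not rise through this route. Inflation needs arms that differ in withdrawal yet have equal true mean depth.

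An analysis plan not shown here might replace the carried value. It could not recover scans that were never taken, because the protocol sends these patients out of the study.

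**Conclusion.** The point holds in limited form. Followed as written, the protocol either carries forward an earlier depth for patients withdrawn for worsening or complications, or rejects them. Both lose the worsening from the primary analysis, and rejection also contradicts the Discontinuation rule and the stated intention-to-treat analysis.

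The likely size is modest: 0.10 SD for a 10-point difference in loss with a 1 SD gap, and 0.05 to 0.225 SD over the assumed range. The sign is open, and the carry-forward error is zero if shares and gaps are equal across arms. These figures rest on assumed loss rates and gaps, and on reading the last recorded data as carry-forward. The conflict between sections rests on the text alone.

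**What to change.** 1. Reconcile Rejection, Discontinuation, Dropout, Adverse events and Statistical analysis so that every randomised patient stays in the primary analysis and one rule applies to each kind of departure. State whether the assessment after the last treatment includes a depth scan at early stopping.
2. Separate stopping the cataplasm from leaving the study. Patients who stop treatment keep the depth scans already scheduled unless they withdraw consent.
3. Replace the last-recorded-data rule with a likelihood-based repeated-measures analysis of all observed depths.
4. That model assumes data missing at random. A patient with only a baseline depth is in effect predicted from the course of the arm, so a worsening patient could be treated as improving. Add a sensitivity analysis, fixed before unblinding, that assigns an unfavourable depth to those withdrawn for worsening or complications.

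None of this alters when treatment is stopped. The cost is revised wording, already scheduled ultrasounds in a few patients and one extra analysis. Trial status reports 78 subjects against a target of 82, so the retained scans can reach only patients who have not yet finished. The analysis changes can cover everyone if made before unblinding.
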